### Possible Harms

Several meta-analyses show that internet-based programs might be beneficial for college students [41] and that there are no indicated risks to internet-based programs. Moreover, individual patient data meta-analyses showed that participants who received an internet-based program for depression had a lower risk of clinical deterioration when compared with the control group [20,42]. These findings seem to indicate minimal to no risk of possible harm. However, in the event that a participant shows signs of more severe mental health problems, which include but are not limited to self-harm or suicidality, in their responses to the questions in the intervention, the protocol for (emerging) crisis situations will be applied: the e-coach (under the supervision of and in collaboration with a certified mental health care psychologist) will reach out and assess the student’s current situation in more detail through the platform. In cases of mild to moderate risk of a worsening of psychological symptoms, we will advise the student to seek professional help aside from participating in the study. In cases of high risk, we advise the student to seek out professional help and resolve the current situation before continuing participation in the study.

### Platform

The intervention is embedded within the Caring Universities platform. This platform was developed by Caring Universities specifically to deliver eHealth interventions to college students. The platform allows researchers to create interventions, add and arrange the contents (eg, text and visuals), and add questionnaires. Students of participating universities can freely register for the intervention by creating an account on their device (eg, computer or mobile phone). Participants can log into the platform to view its contents 24-7 for a total duration of 2 years, even upon completion of the program. During registration, each participant is presented with a random selection of 3 e-coaches out of all available coaches to choose from based on a name, short biography, and profile picture. Within the platform, participants and e-coaches can interact using textual messages. The platform complies with the General Data Protection Regulation (GDPR) guidelines.

### Assessment Measures

#### Primary Outcomes

##### Satisfaction With the Intervention

To measure participants’ satisfaction with the overall intervention, the Client Satisfaction Questionnaire–8 (CSQ-8) [43] is used. The CSQ-8 is commonly used to measure satisfaction with web-based interventions. It consists of 8 items on a 4-point scale with a total score ranging from 8 to 32, where a higher score indicates greater satisfaction. The CSQ-8 showed high reliability and validity for web-based interventions [44]. Similar properties were found in the Dutch translation of the CSQ-8 [45].

##### Usability

The System Usability Scale–10 (SUS-10) [46] is used to measure the usability of the intervention. It consists of 10 items on a 5-point Likert scale, with a total score ranging from 0 to 40. Total scores are then multiplied by 2.5 to achieve a total score of 0 to 100, where a higher score indicates greater usability. The SUS-10 has become the most widely used standardized questionnaire to assess perceived usability and has shown good psychometric properties (reliability and validity) [47]. The Dutch translation of the SUS-10 has previously been used [48], though publications on its specific psychometric properties could not be found. However, several other translations of the SUS-10 were found to have similar psychometric properties as the English version [47].

##### Adherence

Adherence refers to “the degree to which the user followed the program as it was designed” [32]. This study measures adherence by dividing the number of main modules completed by a participant at the time of posttest by the total number of main modules in the program and multiplying this by 100. The resulting percentage will indicate the completion rate. Participants who have not completed a single module will be excluded from these analyses as they did not start the treatment.

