### Intervention

The guided eHealth program aimed at reducing procrastination behavior (GetStarted) is developed based on the principles of CBT. Students are involved in the development of the program by giving their opinions and feedback on the program content as well as the layout of the website that contains the program. The feedback is implemented to ensure that GetStarted meets students’ needs and preferences.

GetStarted (Figure 1) consists of 9 modules, of which 5 are mandatory main modules and 4 are optional modules. The modules consist of psychoeducation, reflective questions, interactive exercises, and homework assignments. The content is delivered both textually and visually, including through the use of pictures, infographics, and videos. Each module takes approximately 30 to 45 minutes to complete, and students are advised to complete 1 main module a week. The duration of the program will therefore be approximately 4-5 weeks, though students are allowed to go at their own pace and can access the intervention for 2 years. Students will be able to access the program from any device that allows internet access.

The first module offers an introduction to the program and its contents. Students are recommended to continue with the second module right away, which covers information on the psychological processes behind procrastination. The third module will allow students to identify the negative thoughts and feelings that accompany certain tasks, causing them to procrastinate. The fourth module will contain a cognitive restructuring exercise in which they will challenge their negative thinking patterns. The fifth and final main module will let the student reflect on their progress, prepare for the future, and include a summary of all the modules.

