**Figure 1 figure1:**
[figure not shown]
Screenshot of GetStarted, an eHealth intervention targeting procrastination.

In addition to the main modules, students will be able to choose to do 1 or several of 4 optional modules. The topics of the optional modules will be (1) breaking a big task into smaller parts; (2) creating and sticking to a plan; (3) motivational techniques; and (4) increased productivity. All optional modules will become available upon completion of the second main module.

The intervention will be created based on the following principles of optimized user interface [40] in collaboration with a user experience designer: a menu containing several main sections, presentation of content in small chunks, stepwise exercises with separate instructions at each step, examples presented in expandable containers, and showing responses given by the participant in previous exercises when relevant.

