### Sample Size

There is no clear method to calculate the sample size of an open feasibility study. Studies have suggested sample sizes ranging from at least 12 participants [60,61] to 35 or more participants [62]. In this study, no power calculation was conducted to determine the sample size, as the main focus is on the feasibility and acceptability of the intervention. Based on these rules of thumb and similar previous studies [63], we anticipate that a minimum of 50 participants will be sufficient to examine our main objectives. However, as the intervention will remain accessible to students for several years as part of the service offering of the Caring Universities project, we anticipate more than 50 participants will make use of the intervention. We will analyze the data of all participants who have used the intervention at the time of data analysis to be able to draw stronger conclusions.

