#### Adherence

A recent meta-analysis looking at internet interventions for mental health among university students found dropout rates between 11.84% and 50.33% [65]. Given the nature of procrastination, dropout is expected to be on the higher side. We will consider the intervention a success if adherence reaches 50%.

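### The 50% adherence criterion is judged only on students who completed at least one module, so it overstates adherence among all enrolled students

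*Protocol article*

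**What the plan says.** The Adherence paragraph under Primary Outcomes obtains each student's score as follows: "dividing the number of main modules completed by a participant at the time of posttest by the total number of main modules in the program", times 100. It then removes part of the sample: "Participants who have not completed a single module will be excluded from these analyses as they did not start the treatment".

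The Intervention section gives the denominator: "GetStarted (Figure 1) consists of 9 modules, of which 5 are mandatory main modules and 4 are optional modules". It describes the opening module as follows: "The first module offers an introduction to the program and its contents". On the optional modules it says: "All optional modules will become available upon completion of the second main module".

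The Adherence paragraph under Statistical Analysis cites a meta-analysis of internet interventions in university students that "found dropout rates between 11.84% and 50.33" per cent. It expects this trial to lie towards the upper end, and sets the rule: "We will consider the intervention a success if adherence reaches 50" per cent.

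The article provides for no adherence figure that counts students with no completed module, no report of how many there are, and no limit on their share.

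**The concern.** The exclusion selects on the outcome itself. Adherence is defined as the degree to which the programme was followed. Zero modules is the lowest value on that scale, and it is the only value taken out before the result is compared with 50%.

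The reason given does not fully carry the rule. A student who opens the first module and abandons it has started but not completed, and is excluded all the same.

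The excluded group matters for this trial's question. The Introduction and the limitations section both warn that procrastination may worsen nonadherence, and the Conclusions ask whether students who procrastinate will adhere. Students choose an e-coach at registration, and coaches send reminders to inactive participants. If this support does not lead to even one completed module, that failure is absent from the adherence result. One of the three success statements could then be read as covering all enrolled students when it covers only those who got past the introduction.

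**Working it through.** **Inputs from the article.** There are 5 main modules, so one module is worth 20 percentage points. Students with 0 completed modules are excluded. The criterion is 50%.

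**Assumptions.** The share of enrolled students with no completed module, p0, is not given and is varied from 10% to 50%. I read the criterion as applying to the mean completion percentage, and I take the exclusion to be judged at posttest, when modules are counted.

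**Step 1: the plan's own figure.** The 50% is a chosen cut-off, not the result of a power calculation. It lies close to the complement of the highest cited dropout rate: 100 − 50.33 = 49.67.

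**Step 2: the floor.** An analysed student has at least one completed module. It must be a main module, because the optional ones open only after the second main module. The lowest possible score is 1/5 × 100 = 20%.

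**Step 3: what 50% requires.** It is a mean of 0.50 × 5 = 2.5 modules. The inclusion rule guarantees the first, so 1.5 of the other 4 are needed: 1.5/4 = 37.5%. For example, the criterion is met if 37.5% of analysed students finish all five modules and 62.5% stop after the introduction: 0.375 × 100 + 0.625 × 20 = 37.5 + 12.5 = 50.

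**Step 4: translation to all enrolled.** With excluded students scored 0%:

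adherence among all enrolled = (1 − p0) × adherence among those with at least one module.

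| Assumed p0 | All-enrolled adherence when the reported figure is 50% | Reported figure needed for 50% among all enrolled |
|---|---|---|
| 10% | 0.90 × 50 = 45% | 50/0.90 = 55.6% |
| 20% | 0.80 × 50 = 40% | 50/0.80 = 62.5% |
| 30% | 0.70 × 50 = 35% | 50/0.70 = 71.4% |
| 40% | 0.60 × 50 = 30% | 50/0.60 = 83.3% |
| 50% | 0.50 × 50 = 25% | 50/0.50 = 100% |

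Above p0 = 50%, no result among the analysed students could give 50% among all enrolled.

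**Step 5: full completion in the Step 3 example.** The share of enrolled students who finish the programme would be 0.375 × 0.70 = 26.25% at p0 = 30%, and 0.375 × 0.50 = 18.75% at p0 = 50%.

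**The case against.** The strongest defence is that this is a different target, not an error. Conditioning on a first completed module separates adherence from uptake. The rule is prespecified, explained and visible, and it validly estimates adherence in the group it describes. All of that stands, and it is why the prespecified figure should be kept. It does not justify resting the feasibility verdict on that figure alone.

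Two further defences have partial force:
- **Timing.** Modules are counted at the 4-week posttest, while the programme is expected to take 4 to 5 weeks and access lasts 2 years. Some zeros may be late starters, and some students on schedule may be counted as incomplete. Measured against eventual completion, the net direction of error is not established. Both figures share the same time point, however, so timing does not close the gap between them.
- **Benchmark.** The article does not say whether the cited dropout rates are based on all enrolled or only on starters. The 50% mark therefore cannot be shown to belong to either denominator, which is a reason to report both.

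The documents do not support two stronger readings that a reader might infer:
- **A contradiction with the Sample Size section.** That section says: "We will analyze the data of all participants who have used the intervention at the time of data analysis". It does not define use, and it can be read consistently with a rule of at least one completed module.
- **A non-start share taken from the Results.** By May 2023, 985 had enrolled and 372 had completed the posttest, leaving 613 (62.2%) without one. These students are not known to have completed no module, and some may not yet have been due, so 62.2% cannot stand in for p0.

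**Conclusion.** The point holds as one of scope. The adherence figure is valid for students who completed at least one module. It overstates adherence among enrolled students whenever anyone completed none. Its floor is 20%, given that exclusion is judged at posttest.

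The size depends on an unknown share. The gap at the 50% mark is modest if 10% completed none (45% among all enrolled) and substantial at 30% or more (35% or below). A reader might conclude that adherence among enrolled students is far below the reported figure. The article does not show this; it shows only that the criterion could be met in that situation without the report revealing it.

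This should be fixed. The primary analyses are descriptive and the rule is openly stated, but as written the success statement can reach further than the students it was measured on.

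**What to change.** **Adherence, under Primary Outcomes.** Add an adherence figure for all enrolled participants, with zero completed modules scored as 0%. Report it beside the prespecified figure for those with at least one completed module, together with the share who completed none. State who counts as enrolled. Describe the excluded students as not having completed a module, not as not having started.

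**Adherence, under Statistical Analysis.** Claim adherence success for enrolled students only if the all-enrolled figure reaches 50%. If only the prespecified figure does, limit the conclusion to students who completed at least one module.

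**Cost.** A few sentences and one more descriptive figure, based on the module counts that the outcome already uses. The prespecified definition stays in place, which matters because recruitment began in January 2021. The downside is that the reported adherence will look less favourable.

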#### Secondary Outcomes

##### Procrastination Tendencies

The IPS is used to assess procrastination tendencies [49,50]. This scale contains 9 items on a 5-point Likert scale. The scale aims to assess the extent to which participants procrastinate. Higher scores indicate higher levels of procrastination. The IPS is used to assess the changes from pre- to postscores. The IPS showed good internal consistency (Cronbach α=.91) [50] as well as a high level of reliability (*r_pm_*=0.58-0.74), and good content, structural, and substantive validity [51].

##### Depressive Symptoms

Depression is assessed with the Patient Health Questionnaire–9 (PHQ-9) [52]. It consists of 9 items on a 4-point Likert scale, with a total score ranging from 0 to 27. Higher scores indicate higher levels of depression. The scores of 0-4, 5-9, 10-14, 15-19, and 20-27 are indicative of no depression, mild depression, moderate depression, moderately severe depression, and severe depression, respectively [52]. The PHQ-9 was found to have high sensitivity (0.71-0.84), specificity (0.90-0.97), internal consistency (Cronbach α=.86-.89), test-retest reliability (*r*=0.84), and validity [53,54].

##### Perceived Stress

Stress levels are assessed using the Perceived Stress Scale–10 (PSS-10) [55,56]. This self-report scale consists of 10 items on a 5-point Likert scale with a total score ranging from 0 to 40, where a higher score indicates higher perceived stress. The PSS-10 was found to have high validity, internal consistency (Cronbach α=.74-.91), and test-retest reliability (*r*=0.74-0.88) [56,57].

##### Quality of Life

Quality of life was measured using the Mental Health Quality of Life questionnaire (MHQoL) [58]. It contains 7 items on a 4-point Likert scale that cover the dimensions of self-image, independence, mood, daily activity, physical health, relationships, and future. The total score ranges from 0 to 21, where a higher score indicates a better quality of life. The MHQoL was found to have good validity, test-retest reliability (*r*=0.85), and internal consistency (Cronbach α=.85) [58].

##### Digital Coach Evaluation

The Working Alliance Inventory for guided Internet interventions (WAI-I) [59] is used to evaluate participants’ satisfaction with the e-coach. The WAI-I consists of 12 items on a 5-point Likert scale with a total score ranging from 12 to 60, where higher scores indicate higher satisfaction. The psychometric characteristics of the WAI-I yielded adequate results [59].

#### Additional Measures

The following sociodemographic information is collected to examine sample characteristics: age, gender, marital status, nationality, attending university, faculty, education level (bachelor, master’s, or PhD), and whether psychotherapy and medication are received.

#### Assessments

An overview of the assessments can be seen in Table 1.

**Table 1 table1:** Measures and assessment points.

Measures	Assessment points		
	T0^a^	T1^b^	T2^c^
Sociodemographic	✓		
Client Satisfaction Questionnaire (CSQ-8)		✓	
System Usability Scale (SUS-10)		✓	
Irrational Procrastination Scale (IPS)	✓	✓	✓
Perceived Stress Scale (PSS-10)	✓	✓	✓
Patient Health Questionnaire (PHQ-9)	✓	✓	✓
The Mental Health Quality of Life Questionnaire (MHQoL)	✓	✓	✓

^a^Pretest.

^b^Posttest (4 weeks).

^c^Follow-up (6 months).

### Sample Size

There is no clear method to calculate the sample size of an open feasibility study. Studies have suggested sample sizes ranging from at least 12 participants [60,61] to 35 or more participants [62]. In this study, no power calculation was conducted to determine the sample size, as the main focus is on the feasibility and acceptability of the intervention. Based on these rules of thumb and similar previous studies [63], we anticipate that a minimum of 50 participants will be sufficient to examine our main objectives. However, as the intervention will remain accessible to students for several years as part of the service offering of the Caring Universities project, we anticipate more than 50 participants will make use of the intervention. We will analyze the data of all participants who have used the intervention at the time of data analysis to be able to draw stronger conclusions.

### Statistical Analysis

Participants’ satisfaction with the intervention, usability, and adherence will be examined by calculating descriptive statistics.

### Satisfaction

Each of the 8 items on the CSQ-8 has 4 answering options, of which 2 indicate dissatisfaction (scored 1 or 2) and the other 2 indicate satisfaction (scored 3 or 4). Our goal is for participants to be satisfied or very satisfied with the intervention, meaning a score of 3 or 4 per item. This corresponds with an average total score between 24 and 32. We will consider the intervention a success if average CSQ-8 scores reach a minimum of 24.

#### Usability

Bangor et al [64] have found that SUS-10 scores above 70 are passable, with scores above 90 indicating superior products. We will consider the intervention a success if average SUS-10 scores reach a minimum of 70.

#### Adherence

A recent meta-analysis looking at internet interventions for mental health among university students found dropout rates between 11.84% and 50.33% [65]. Given the nature of procrastination, dropout is expected to be on the higher side. We will consider the intervention a success if adherence reaches 50%.

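### The 50% adherence threshold is justified by dropout rates, a share of people, but applied to the percentage of modules completed among starters

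*Protocol article*

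**What the plan says.** Adherence is one of three primary outcomes, each with its own success rule.

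- **Outcome** (Primary Outcomes, Adherence). Each participant's adherence is defined through "dividing the number of main modules completed by a participant at the time of posttest by the total number of main modules in the program", expressed as a percentage. The article adds: "The resulting percentage will indicate the completion rate". On the analysis set it says: "Participants who have not completed a single module will be excluded from these analyses as they did not start the treatment".
- **Success rule** (Statistical Analysis, Adherence). "We will consider the intervention a success if adherence reaches 50" per cent.
- **Justification** (same section). A meta-analysis of "internet interventions for mental health among university students found dropout rates between 11.84% and 50.33" per cent, followed by: "Given the nature of procrastination, dropout is expected to be on the higher side". No other figure is given in support.
- **Programme** (Intervention). There are 5 main modules. The first is an introduction, and of the next step the article says: "Students are recommended to continue with the second module right away". The cognitive restructuring exercise is in module 4 and the closing reflection in module 5. The expected length is about 4-5 weeks, at the student's own pace.
- **Timing** (Study Design). Posttest is 4 weeks after baseline.

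For satisfaction and usability, the success rules are stated in terms of average scores. The adherence rule names no summary statistic, and the opening of Statistical Analysis says only that the primary outcomes will be described.

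**The concern.** A dropout rate counts people: someone has left or has not. The adherence outcome counts modules within people, and then only in people who completed at least one. A figure of 50% on one scale does not carry over to the other, and the article offers no bridge.

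The article says the study will examine whether students who procrastinate adhere to an intervention of this kind. A reader who sees the dropout range beside the threshold will take a pass to mean that about half the students stayed. The module percentage does not show that. Excluding non-starters gives everyone analysed at least 20%, and a student who follows the advice to take the first two modules together has 40%. That is still short of 50%, but it means a pass at the threshold says little about how many students reached the later modules.

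**Working it through.** **Inputs.** Threshold 50% and dropout range 11.84% to 50.33% (Statistical Analysis, Adherence); module percentage among participants with at least one module (Primary Outcomes, Adherence); 5 main modules (Intervention); count taken at posttest, 4 weeks (Study Design). Two assumptions are added: the criterion is a mean, and dropout means not completing all 5 main modules.

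1. **The plan's own figure.** The complement of the highest quoted dropout rate is 100 - 50.33 = 49.67%, or about 50%. The threshold is reproduced as a share of people.

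2. **The scale it is applied to.** With 5 modules and non-starters excluded, a participant can score only 20, 40, 60, 80 or 100%. A mean of 50% is 2.5 modules.

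3. **Most full completers at a mean of exactly 50%.** Let x be the share of starters who complete all 5. It is largest when all the others stop after one module: 100x + 20(1 - x) = 50, so 80x = 30 and x = 37.5%. Non-completion is then 62.5%.

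4. **Fewest full completers at the same mean.** If half complete two modules and half three, 0.5 × 40 + 0.5 × 60 = 50 with no completers. Non-completion is then 100%. If modules are taken in order, nobody has completed module 4.

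5. **Going the other way.** Suppose 50.33% of starters do not complete and all of them stop after k modules. Mean adherence is 49.67 + 0.5033 × 20k:

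| Non-completers stop after | Mean adherence |
|---|---|
| module 1 | 59.7% |
| module 2 | 69.8% |
| module 3 | 79.9% |
| module 4 | 89.9% |
| evenly over modules 1-4 | 49.67 + 0.5033 × 50 = 74.8% |

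No stopping pattern makes a mean of 50% equivalent to 50.33% non-completion among starters.

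6. **Above the threshold.** For a mean of m%, the smallest possible non-completion is (100 - m)/80. This gives 56.25% at m = 55, 50% at m = 60 and 25% at m = 80. The bound of 62.5% therefore belongs to a mean of exactly 50%. Across all passing results, non-completion can lie anywhere from 0% to 100%.

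7. **Role of the exclusion.** If non-starters were kept at 0%, step 3 would become 100x = 50 and the smallest non-completion would be 50%. The rise to 62.5% comes from excluding them. Over all enrolled, with an assumed non-starter share s, non-completion at the threshold is at least 1 - 0.375(1 - s): 66.25%, 70% and 73.75% for s = 10%, 20% and 30%. The article does not give s, so this is only a range.

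**The case against.** The strongest reply is that the contrast depends on two things the article does not say. The first is the statistic. If the 50% were the share of participants who complete, threshold and benchmark would both count people and the mismatch in scale would disappear. The second is the meaning of dropout in the cited meta-analysis. It could be loss to posttest, stopping early, or not finishing every module, and only the last allows 62.5% to be set directly against 50.33%. Timing adds to this. Modules are counted at 4 weeks in a self-paced programme of about 4-5 weeks that stays open for 2 years, so a student on module 4 or 5 at posttest may be on schedule. Finally, this is a single-arm feasibility study with descriptive primary outcomes, and completion can be tabulated from the same counts whatever the rule says.

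Much of this stands and limits the claim. A reader might infer that any declared success implies at least 62.5% non-completion; step 6 shows that this is true only at a mean of exactly 50%. A reader might also infer that the plan accepts a result worse than the worst published one. The documents do not support that as a fact, because dropout is undefined and some non-completers at 4 weeks may still be active. The case with no completers is an extreme, not a forecast.

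The mismatch itself remains. The outcome section defines a per-participant module percentage, for which a mean is the natural summary. Reading the rule as a share of completers would instead mean that it uses a quantity the outcome section does not define. On either reading the two Adherence sections have to be reconciled. Nor is this a detail left to a fuller document: outcome, exclusion, threshold and justification are all stated in the article.

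**Conclusion.** The point holds in a limited form. A decision threshold for a primary outcome is justified on one quantity and applied to another. If the criterion is a mean, reaching exactly 50% is compatible with 62.5% to 100% of starters not having completed all 5 main modules at 4 weeks. This is above the quoted 50.33% only on the further assumption that dropout means not completing the programme.

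The threshold should be corrected before the success rule is applied, because the mismatch changes what a declared success can mean. It does not undermine the study: the data collected are unaffected, and the remaining descriptive results can be reported as planned.

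**What to change.** Put the criterion and its justification on the same scale, in one of two ways.

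- **Person-level criterion (preferred).** Judge success against the dropout benchmark by the proportion of participants who complete all 5 main modules. Use all enrolled participants as denominator and show the same proportion among starters. State a time point that allows for the 4-5 week programme length. State how the cited meta-analysis defines dropout, so that the comparison can be checked. Keep the mean percentage of modules, and the distribution of the last module completed, as descriptive outcomes.
- **Module-percentage criterion.** Keep it, but name the statistic and the denominator, drop the dropout rates as its justification, and report the proportion of full completers beside it.

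Either way, the change is to the two Adherence sections (Primary Outcomes and Statistical Analysis). It needs no new data. The person-level criterion may be harder to meet.
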